# Pilot trial of Stop Delirium! (PiTStop) - a complex intervention to prevent delirium in care homes for older people: study protocol for a cluster randomised controlled trial

**DOI:** 10.1186/1745-6215-15-47

**Published:** 2014-02-05

**Keywords:** Pilot, Feasibility, RCT, Complex intervention, Older people, Delirium, Care home

## Abstract

**Background:**

Delirium (or acute confusion) is a serious illness common in older people, in which a person’s thinking and perceptions may be affected. Reducing delirium is important because of the considerable distress it causes, and the poor outcomes associated with it, such as increased admissions to hospital, falls, mortality and costs to the National Health Service (NHS). Preventing delirium is possible using multicomponent interventions; successful interventions in hospitals have reduced it by one-third. However, there is little research to guide practice in care homes, where it is common because of the clustering of known risk factors (older age, frailty, and dementia). In previous work we developed a multicomponent intervention to prevent delirium in care homes, called Stop Delirium! The intervention was based upon evidence from the research literature relating to the prevention of delirium and on strategies to change professional practice. Before starting a large costly trial of Stop Delirium!, this pilot study will test and help improve the design and feasibility of the trial protocol.

**Methods/Design:**

We plan to conduct a cluster randomised pilot trial in 14 care homes (independent residential and nursing). Following recruitment of residents (over 60 years, consenting or with consultee agreement, able to communicate in English, and not in palliative care) participating homes will be randomised, stratified by size of home and proportion of residents with dementia. Stop Delirium! will be delivered to intervention homes over 16 months, with controls receiving usual care. The primary outcome measure will be the presence of delirium on any day during a one-month post-intervention period.

We will collect data to determine 1) recruitment and attrition rates, 2) feasibility of various outcomes measurements, and 3) feasibility of capturing health resource use (resident diaries and by examining health records). We will estimate the between-cluster variation for the primary outcome, delirium occurrence.

**Discussion:**

This pilot study will refine methods for the definitive trial. The lessons learnt will also contribute to implementing National Institute for Health and Clinical Excellence (NICE) delirium guidelines, which recommend multicomponent interventions for delirium prevention.

**Trial registration:**

ISRCTN27972532.

## Background

Delirium is a distressing but preventable condition that is common in older people. It is associated with increased morbidity, mortality, functional decline, hospitalisation, and significant healthcare costs [1,2]. Despite its high prevalence and poor outcomes, delirium has been under-researched and neglected in clinical practice [1,3]. Most research on delirium has focused on hospital patients. Another (expanding [4]) high risk group is residents of care homes for older people. The burden of delirium is likely to be considerable in residents of long-term care given the clustering of known delirium risk factors [5], especially the high prevalence of dementia. Individuals admitted to hospital from long-term care have higher rates of delirium [6], and institutional residence has been identified as a risk factor for post-operative delirium [7]. However, there have been few good-quality studies, investigating delirium in long-term care. A systematic review [8] found no studies of delirium incidence and no studies from the United Kingdom (UK). The median point prevalence of delirium was reported to be 14% in studies reflecting the UK model of long-term care [8].

We know that delirium can be prevented (reduced by one-third) in hospitals [9-11]. Successful interventions are multifaceted and rely on a combination of staff education and systematic screening for modifiable risk factors (attending to dehydration, pain, sensory impairments and poor mobility). These are areas of care that should be equally applicable to long-term care settings. It is not yet known, however, whether a similar approach might be effective in care homes. The recent National Institute for Clinical Excellence (NICE) delirium guideline recommends that such interventions should be implemented in long-term care given the likely benefits. In addition, it recommends that the clinical and cost effectiveness of these interventions should be investigated as a research priority [12].

A further reason to focus on delirium is its link to care quality [13], which has been a subject of concern for some time in long-term care [14,15]; training of staff has not kept pace with the changing demands of care homes [16,17], and there is poorer management of medical conditions, increasing the need for unplanned hospital admissions and general practitioner (GP) consultations [18]. Achieving improvements in care quality is challenging [19]. Optimum delirium care is fundamentally the provision of basic good quality supportive care [13]. For staff inured to endless messages to improve quality, a focus on delirium prevention may be the ‘Trojan horse’ through which this can be achieved [20]. There are additional potential benefits: reducing morbidity, hospital admissions and healthcare costs.

In previous work, we used the Medical Research Council (MRC) framework for the development of complex interventions [21] to design the ‘Stop Delirium!’ [22] intervention to prevent delirium in care homes.

The Stop Delirium! intervention - essentially an enhanced educational package for care home staff - incorporates strategies to change practice, such as adapting to the local context, interactive teaching methods, promoting ownership and championing. This approach to delirium prevention is based upon and supported by the research literature from hospital settings and is consistent with NICE guidelines.

In preparation for this pilot trial, we have developed a standardised Stop Delirium! toolkit including a manual for the Delirium Practitioner and educational resources for care home staff.

Each of the intervention elements is discrete but interlinked. The individual components of Stop Delirium! are shown in Figure 1. We have now initiated a pilot trial as the first stage in an evaluation programme for this complex intervention. A flowchart of the trial procedure is shown in Figure 2.

**Figure 1 F1:**
[figure not shown]
The individual components of Stop Delirium!

**Figure 2 F2:**
[figure not shown]
Flowchart of the PiTStop trial procedure.

### Aims and objectives

The primary hypothesis for the main trial will be that Stop Delirium! is a cost-effective way to prevent delirium episodes in residents of older people’s care homes. The secondary hypothesis will be that this will lead to a reduction in admissions to hospital from this population. The main objective of this pilot trial is to gather process, management, resource and scientific data to inform the design of a definitive trial. The principle objectives of this pilot and the corresponding research questions are outlined in Table 1.

**Table 1 T1:** Principle objectives, research questions and outcomes

**Principle objectives**	**Research questions**	**Outcomes**
**Process:** To provide an estimate for the number of care homes needed for the main trial	What are the potential recruitment and attrition rates for enrolment of residents?	
**Resources:** To investigate the acceptability of the proposed measurements to residents and the most appropriate informant	Which type of data collection diaries (care home resident level), designed by the team to capture health and social care resource use, are most acceptable to residents and staff (>75% completed)? And are these diaries valid (contain information that can be used to calculate costs)?	Activities of daily living Number of falls during previous 6 months
		Mortality during previous 6 months
		Hospital admissions during previous 6 months including total length of stay; number of admissions; time to first admission
		Health-related quality of life
	Which health-related quality of life measure, the EuroQol (EQ-5D 3 L) [23], ASCOT Social Care-Related Quality of Life (SCRQoL) [24] or the DEMQOL-V4 [25] is more acceptable to residents (greater % of questionnaires completed)? And are resident and proxy reports of HRQoL comparable?	
	Are baseline and outcomes measures outcome rates adequate (achieving >75% complete data for each)? And what resources are required in determining these outcomes?	
**Management:** To assess the adherence to, and sustainability of Stop Delirium!	What are the adherence rates for the various components of the intervention? And what are the facilitators and barriers for sustainability and integration into routine care, after the intervention?	Total number of medications Health related quality of life Health and social care costs as measured by health related quality of life measures and health and social care resource use
	What are the costs from the perspective of the service provider (health and social care) associated with delirium and with Stop Delirium?	
**Scientific:** To determine the most appropriate method to capture resource use in this setting and population and costs of delirium and of delivering the intervention	Can a high (>90%) coverage for delirium screening be achieved using the short Confusion Assessment Method (CAM) [26]? And can a high completion rate (>90% complete) be achieved for the Delirium Rating Scale-Revised (DRS-R-98) [27] in those positive for CAM? Is delirium be determined reliably (>90% inter-rater reliability) using these instruments?	Delirium severity: proportion of residents with severe delirium during a one-month period
		Delirium duration (days positive for delirium) during a one month period
		Delirium incidence on any on any day during a one-month post-intervention period
		Mortality during previous 6 months
		Hospital admissions during previous 6 months including total length of stay, number of admissions, time to first admission
	What are the rates of delirium and admission to hospital in residents in intervention homes compared to control homes post intervention? And which measure yields more complete hospital admission data: length of stay, number of admissions or time to admission?	
To estimate the rates of delirium and hospital admissions in intervention and control homes	What is the intraclass coefficient (ICC) for the proposed primary outcome, delirium occurrence?	The primary outcome for this study is the presence of delirium on any day during a one-month post intervention period determined by screening with short version CAM [26] on alternate days (except Sundays) and confirmed for those positive or borderline using the Delirium Rating Scale-98 (DRSR98) [27].

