#### Outcomes for the economic evaluation

Health and social care use by residents will be recorded using specifically designed data collection forms/diaries. Data will be collected at 4, 8 and 16 months from randomisation. Contemporaneous study records (of salaries and travel expenses) will be kept to determine resource use in implementing the intervention. We will collect the bulk of resource use data from care home records but will test the accuracy of this method by comparing the results with those from a subset of individual resident care records and with centralised records of events, such as hospitalisation from the Health and Social Care Information Centre (HSCIC).

Unit financial costs for health and social care resources will be obtained from national sources (Personal Social Services Research (PSSRU) Unit Costs of Health and Social Care, British National Formulary (BNF) and NHS reference cost databases) and used to determine costs. Utility (HRQoL) values will be determined from either EQ5D-3 L, SCR QoL or DEMQOL-P-4D.

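### Diary validity is defined as costability, and the only stated accuracy check is on care-home-record data, so the choice of resource-use method is informed by accuracy for one route only

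*Protocol article*

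**What the plan says.** The Abstract (Methods/Design) names two routes when it sets out to examine the "feasibility of capturing health resource use (resident diaries and by examining health records". Table 1, under Aims and objectives, includes the objective "To determine the most appropriate method to capture resource use in this setting and population".

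For diaries, Table 1 gives two criteria. The first is acceptability: which diary types "are most acceptable to residents and staff (>75% completed". The second is validity: "And are these diaries valid (contain information that can be used to calculate costs".

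Outcomes for the economic evaluation first says "Health and social care use by residents will be recorded using specifically designed data collection forms/diaries", at 4, 8 and 16 months from randomisation. It then says: "We will collect the bulk of resource use data from care home records but will test the accuracy of this method by comparing the results". The comparators are a subset of residents' own care records and central (HSCIC) records of events such as hospitalisation.

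**The concern.** Whether an entry can be costed and whether it is true are different properties. A diary with dated, itemised contacts can be costed in full and still omit half of what happened. The authors plainly distinguish the two, because they plan an accuracy check for the care-home-record data. The diary criterion carries the word valid but tests neither agreement nor omission.

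This matters because the pilot exists to settle methods for a definitive trial whose primary hypothesis, under Aims and objectives, is about cost-effectiveness. If diaries were carried forward after meeting the Table 1 criteria, cost estimates built on them would rest on an instrument whose accuracy had not been reported. Blinding states that participants cannot be blinded, so recording could also differ between arms, and neither diary criterion would show it.

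**Working it through.** The plan has no figure to reproduce here, so the check sets the stated criteria side by side.

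| Property | Diaries | Care home records |
|---|---|---|
| Completion | Above 75% (Table 1) | No separate threshold; the general Table 1 threshold of above 75% for baseline and outcome measures may apply |
| Can be costed | Yes, labelled validity (Table 1) | Not stated |
| Agreement with a reference | Not stated | Yes, against a resident-record subset and HSCIC records (Outcomes for the economic evaluation) |

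In the sentence "We will collect the bulk of resource use data from care home records but will test the accuracy of this method by comparing the results", the method under test is collection from care home records. Data quality does not extend the check: it covers completion and inter-rater reliability of the delirium instruments, and which hospital-admission variable is most complete.

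**Illustration of what the diary criteria let through.** The inputs are assumptions, not figures from the article. Let *c* be the share of diaries completed and *e* the share of true events entered in a completed diary. If uncompleted diaries yield nothing and events are equally frequent in both groups, the share of events captured is *c* × *e*.

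- *c* = 0.80, *e* = 0.60: 0.80 × 0.60 = 0.48
- *c* = 0.80, *e* = 0.80: 0.80 × 0.80 = 0.64
- *c* = 0.90, *e* = 0.95: 0.90 × 0.95 = 0.855

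All three exceed 75% completion, and all three would be called valid if the entries made can be costed. Capture ranges from 48% to 85.5%, and the Table 1 criteria do not separate the cases.

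**Period over which a check is possible.** Diary data are collected at 4, 8 and 16 months. Outcome assessments says admission events before month 10 were not collected, so the planned admission outcome covers 16 − 6 = 10 to 16 months. The collections at 4 and 8 months fall wholly before that window. A three-way comparison of diary, care-home-record and central admissions is therefore confined to months 10 to 16.

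**The case against.** The strongest reply is that the two routes may not be rivals. The economic section mentions forms or diaries and then says most data come from care home records; the forms may simply be filled in from those records, in which case the accuracy check already covers most of their content. The diary question in Table 1 also compares types of diary with each other, and the objective on the most appropriate method sits in a different row, beside delirium-screening questions, perhaps because the table was disturbed in extraction. This stands in part: the text is ambiguous. But the Abstract lists diaries and records as two means of capture, and Table 1 judges diaries on acceptability to residents and staff, which suggests an instrument in its own right. On either reading a clarifying sentence is needed.

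A second reply is that a condensed article leaves such detail to the full protocol. That would excuse silence on how sources are reconciled. It does not cover a validity definition that the article prints and that does not test accuracy.

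A reader might infer that the two routes share no yardstick, so that no method can be chosen. The documents do not support that. Completeness is a possible common measure, and Analysis describes a descriptive pilot that can weigh acceptability, completeness, costability and accuracy without a formal rule. A reader might also infer that nothing would reveal a diary that misses admissions. That is wrong too: Post-intervention assessments takes admissions from care home and hospital records, and HSCIC records are planned, so the omissions could be seen if someone looked. The article does not say that anyone will.

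**Conclusion.** The point holds in a narrow form. Diary validity is defined by usability alone, the stated accuracy check belongs to care-home-record data, and the objective of choosing a capture method would be informed by accuracy for one route only. The size of any under-recording cannot be derived from the article; the 48% to 85.5% range shows only that very different levels of capture meet the same criteria. The conclusion assumes that the diaries are at least partly a separate source. If they are transcribed from care home records, the defect reduces to one of wording. Severity is minor: this is a pilot, most resource-use data come from the route that is checked, and the reference data are already planned.

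**What to change.** 1. In Table 1, keep the costability question but label it usability. Define diary validity as agreement with the reference sources already named under Outcomes for the economic evaluation.
2. For residents with both sources, compare admissions and bed-days from diaries and from care home records with the central hospitalisation records over the overlapping period, months 10 to 16. Compare other contacts with the planned subset of residents' own care records.
3. Report agreement descriptively by arm, and say that it will be weighed alongside completion when the method is chosen.
4. If the forms or diaries are completed from care home records, say so and state that the existing accuracy check covers them.

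The cost is a change of wording and a little more analysis. Baseline assessments already lists the NHS number, and both reference sources are planned. Two limits remain. Admissions before month 10 cannot enter the three-way comparison. The central records are described only as covering events such as hospitalisation, so social-care use can be checked only in the resident-record subset, whose size the article does not give.

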#### Resident data

Screening and baseline data for residents will be collected before randomisation. Post-intervention outcome data will be collected at 16 months post-randomisation.

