### Baseline assessments

For all residents recruited, the following information will be recorded through examining care home records or administering tests. Baseline assessment data will include:

1. Initials

2. NHS number and hospital ID

3. GP name and address

4. Age

5. Sex

6. Medications - total number and names

7. Co-morbidities (Charlson index [30])

8. Activities of Daily Living (ADL) [31]

9. Hearing Impairment

10. Visual impairment (Snellen test card at 3 meters, acuity below 6/18 assessed as visually impaired)

11. EuroQoL EQ-5D and EQ5D proxy [23]

12. Either the Social Care Related Quality of Life (SCR-QoL) [24] or Dementia Quality of Life DEMQOL and DEMQOL-Proxy [25]

13. Delirium

Delirium assessments will be undertaken using a three step process:

1. Assessment of cognitive impairment using the Six Item Cognitive Impairment Test (6-CIT) [32,33]

2. Short Confusion Assessment Method (CAM) [26]

3. In those screening positive on CAM, the Delirium Rating Scale Revised-98 (DRS-R-98) [27] (using a cut-off score of >17.75)

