### Trial governance

A multidisciplinary Implementation Team will guide the operational management of the trial, with responsibility for overall supervision of the study on behalf of the trial sponsor (Bradford District Care Trust) and trial funder (NIHR). The team comprises lay representatives, statisticians, health economists, trial managers, consultants in older people’s care, and experts in complex interventions and qualitative studies. In addition, an independent Advisory Board, chaired by the National Clinical Director for Older People, and including two lay representatives, two care home managers (independent of sample), experts in older people’s care and care homes, will oversee the trial. The primary role of the Advisory Board is *‘to ensure that the rights, safety and well-being of the trial participants are the most important considerations, and prevail over the interests of science and society.’*

This trial is being conducted in accordance with the principles of Good Clinical Practice and the NHS Research Governance Framework and all data are held in accordance with the Data Protection Act and Caldicott principles.

The study protocol received ethical approval from the Yorkshire and Humber Research Ethics Committee on 24/01/2012 (ref: 12/YH/0018). Further approval was given for additional recruitment and a change of quality of life assessment tool on 11/02/2013.

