## Discussion

We have made the following modifications to the original planned protocol: i) increased the number of homes to be included from 12 to 14; ii) included residential as well as nursing homes; iii) introduced additional recruitment of residents at 12 months post-randomisation of homes (2 to 4 months before the post-intervention outcomes assessments); and iv) replaced the SCRQoL with the DEMQOL at post-intervention data collection. These changes will help us investigate the feasibility of alternative approaches to recruitment and quality of life assessments. Modifications have been agreed on by the study sponsor and funder, and have received Ethics Committee approval.

Although yet to be confirmed by the results of this pilot trial, we anticipate that the definitive trial will have a shorter intervention period (between 10 to 16 months), that recruitment of residents will take place nearer to the outcome assessments, and that an alternative method of delirium screening will be used.

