## Trial status

Recruitment is ongoing. The second stage of recruitment started in May 2013.

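### SCRQoL and DEMQOL are to be ranked by raw completion percentage, although one replaced the other between visits, so the ranking is confounded with visit, attrition and recruitment stage

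*Protocol article*

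**What the plan says.** Under Aims and objectives, the Resources row of Table 1 asks which of three quality-of-life measures (EQ-5D, SCRQoL, DEMQOL) "is more acceptable to residents (greater % of questionnaires completed"). The metric is fixed, and all three tools fall under it.

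The schedule is spread over several sections:

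- **Baseline assessments** lists "EuroQoL EQ-5D and EQ5D proxy [23]" for all recruited residents, and separately "Either the Social Care Related Quality of Life (SCR-QoL) [24] or Dementia Quality of Life DEMQOL and DEMQOL-Proxy [25]".
- **Discussion** lists among the modifications that the trial "replaced the SCRQoL with the DEMQOL at post-intervention data collection". It presents the modifications as a help in studying alternative approaches to quality-of-life assessment.
- **Resident data** puts baseline before randomisation and states: "Post-intervention outcome data will be collected at 16 months post-randomisation".
- **Trial governance** records: "Further approval was given for additional recruitment and a change of quality of life assessment tool on 11/02/2013". **Trial status** adds: "The second stage of recruitment started in May 2013".
- **Resident recruitment** explains that the second stage was added because attrition is expected in a very frail population. It takes in residents who arrived after the first round, once homes had been allocated.

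**The concern.** The criterion treats the three completion percentages as comparable. Two of them come from different visits and, to a large extent, different people. If DEMQOL shows a higher or lower percentage than SCRQoL, the reason may be the tool. It may equally be that the residents assessed at 16 months are the survivors of the first cohort plus newcomers, seen later and after allocation.

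The pilot exists to inform the design of a definitive trial, and the choice of quality-of-life measure is one of its stated questions. A confounded ranking could steer that choice. This is a conflict between a stated metric and a stated schedule, not a missing analysis detail.

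**Working it through.** The plan gives no figure to reproduce, so the check sets the sections side by side and then illustrates the mechanism.

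**Step 1: who supplies each percentage.**

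| Tool | First-stage baseline | Second-stage baseline | 16 months |
|---|---|---|---|
| EQ-5D | Listed | Listed (same assessments as earlier recruits) | Implied by Table 1 and the economic section, not stated outright |
| SCRQoL | Yes, as the tool later replaced | Unclear | Replaced |
| DEMQOL | No joint use with SCRQoL described | Possible: the change was approved on 11/02/2013 and this stage began in May 2013 | Yes |

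No section describes both SCRQoL and DEMQOL being given to one resident at one visit, or a random or balanced assignment between them. If second-stage residents had DEMQOL at baseline, the tool is tied to recruitment stage as well as to visit. The confounding remains on either reading.

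**Step 2: whether the plan deals with it.** The sensitivity analysis under Outcome assessments looks at the impact of the later recruitment phase. It does not separate instrument from visit.

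**Step 3: illustration. All rates are assumptions, since the document gives none.** Suppose SCRQoL and DEMQOL are equally acceptable to any given resident. Let completion be a in cognitively more able residents and b in the others, and let the more able share be m_B at baseline and m_F at follow-up.

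- Completion at a visit = m × a + (1 − m) × b
- Apparent instrument difference = (m_F − m_B) × (a − b)

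Take m_B = 0.60.

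| a / b | Baseline | Follow-up, m_F = 0.40 | Follow-up, m_F = 0.80 | Spurious difference |
|---|---|---|---|---|
| 85% / 40% | 67% | 58% | 76% | −9 to +9 points |
| 80% / 50% | 68% | 62% | 74% | −6 to +6 points |
| 75% / 65% | 71% | 69% | 73% | −2 to +2 points |

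First row worked: baseline 0.60 × 0.85 + 0.40 × 0.40 = 0.67; follow-up at m_F = 0.80 is 0.80 × 0.85 + 0.20 × 0.40 = 0.76; difference 0.09 = 0.20 × 0.45.

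The share could move either way: deaths may remove the less able, while survivors may decline and newcomers may differ. The sign cannot be predicted.

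**Step 4: how far EQ-5D can bridge the visits.** The indirect contrast is (DEMQOL − EQ-5D at follow-up) − (SCRQoL − EQ-5D at baseline). It cancels the case-mix shift only if that shift moves EQ-5D completion as much as it moves the other tools. Suppose EQ-5D follows the 75% / 65% row, the others follow the 85% / 40% row, and m_F = 0.80. The contrast is then (76 − 73) − (67 − 71) = 3 + 4 = 7 points, again with no true difference between SCRQoL and DEMQOL. The same-visit comparisons with EQ-5D are sound in themselves; the indirect contrast needs its assumption stated.

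**The case against.** The strongest reply is that this is a descriptive pilot. Table 1 poses a question with a metric in brackets, and no section says the higher percentage alone will fix the definitive trial's instrument. The article discloses the swap openly. It also plans to record completion time, reasons for noncompletion and whether resident or proxy answered, all of which help in reading the percentages. Paired intervals for one feasibility question could be left to an analysis plan.

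Much of this stands and limits the weight of the point: it touches one secondary question, not the delirium outcome, the intraclass coefficient or the recruitment estimates. It does not remove the conflict, because a descriptive percentage still misleads when the groups differ and the stated metric is not confined to same-visit comparisons.

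Three stronger readings are tempting, and the document does not support them.

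- A reader might infer that neither SCRQoL nor DEMQOL can show change from baseline, so that QALYs are out of reach. Second-stage residents may have DEMQOL at both visits. The economic section says only "Utility (HRQoL) values will be determined from either EQ5D-3 L, SCR QoL or DEMQOL-P-4D"; the article promises neither QALYs nor change in utility.
- A reader might take the absence of quality of life from the Post-intervention assessments list to mean that it is not collected. Table 1 names it as an outcome and the Discussion places DEMQOL at that visit, so this is at most an editorial inconsistency.
- A reader might measure a spurious shift against the 75% completeness threshold. That threshold belongs to other questions in Table 1, not to this ranking.

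**Conclusion.** The point holds in this form: raw SCRQoL and DEMQOL completion percentages are confounded with visit, attrition and recruitment stage, and the stated metric can favour one tool from case mix alone, in either direction. This rests on the replacement stated in the Discussion and the either-or wording at baseline, and on no assumed rate. The size is unknown; the 2 to 9 points above only show that modest assumptions suffice. EQ-5D against SCRQoL at baseline is not affected. EQ-5D against DEMQOL is not affected wherever both are given to the same residents at one visit, but EQ-5D use at follow-up is inferred, not stated. The change is worth making because it is nearly free and removes a misleading comparison from a stated research question.

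**What to change.** 1. Limit the acceptability comparison to same-visit, within-resident differences in completion against EQ-5D: SCRQoL versus EQ-5D at baseline, and DEMQOL versus EQ-5D wherever both are given. Attach confidence intervals that allow for home.
2. Report SCRQoL and DEMQOL completion by visit and recruitment stage, and state that they will not be ranked directly on raw percentages.
3. If an indirect comparison through EQ-5D is made, state its assumption that time and case mix affect completion of EQ-5D and the other tools equally. This may be doubtful for a dementia-specific tool.
4. Confirm that EQ-5D is collected post-intervention, as Table 1 and the economic section imply.

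Cost: wording only, with no new data if EQ-5D is already collected at follow-up. The downside is that SCRQoL versus DEMQOL receives only an indirect or descriptive answer.
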